### 10.7. Randomization and Masking

Participants will be randomized after the project research team determined that they:

1. Will demonstrate a satisfactory interest in joining lifestyle intervention during the run-in.
2. Will express willingness to continue in the trial.
3. Will meet all inclusion/exclusion criteria.
4. Will provide all baseline data.

After exclusions, 824 participants will be allocated at random in a 1:1 ratio to an intensive lifestyle intervention to promote increased physical activity and dietary modification or to minimal lifestyle advice to the control group. Randomization lists will be generated and supplied by the coordinating center, and staff who will perform the baseline measurements will have no access to the randomization lists. Neither staff delivering the intervention nor participants will be masked to the study arm.

## 10.8 Flow Chart

[figure not shown]

## 10.9 Intervention

The faith-based intervention will combine religious teachings with evidence-based health strategies, comprising the following key components:

### 1. Religious Sermons (Khutbah):

- Imams will deliver sermons during Friday prayers to male participants, while female assistants will conduct group sessions to deliver similar messages to female participants.
- These sessions will emphasize healthy lifestyle practices and incorporate culturally relevant religious principles to inspire behavioral change.

- To support their engagement, Imams and their female assistants will be incentivized with payments for their participation in delivering the sermons.
- 2. Diet and Lifestyle Guidance:**
- Participants will receive practical advice to reduce rice consumption, limit the use of extra salt, oil, and sugary foods, and incorporate more vegetables and fruits into their diet.
  - Visual aids, such as the plate model, will be utilized to illustrate balanced eating habits effectively.
- 3. Physical Activity:**
- Male participants will walk with Imams after morning prayers, while female participants will engage in walking sessions with female assistants after afternoon prayers.
  - The goal will be to achieve at least 30 minutes of daily physical activity.
- 4. Performance Monitoring:**
- Trained volunteers will document participants' dietary patterns, physical activity levels, blood pressure, and anthropometric measurements (including weight, waist, and hip circumference) in individual guidebooks.
  - These records will be reviewed during sessions to discuss progress and set future goals.

Each intervention session will last approximately two hours and will be conducted monthly, supplemented by detailed assessments at 4 and 12 months.

#### Intervention tool development

The following interpersonal education and communication (IEC) materials developed by the DPRL program of BADAS will be used for this purpose-

- Khutbah
- Guidebook including dietary and exercise diary
- Flip chart
- Poster & leaflets

#### Intervention session

Twelve (12) sessions for each subject will be carried out for the next 12 months based on the following schedule-

| Serial | Visits                   | Duration           | Tasks                            |
|--------|--------------------------|--------------------|----------------------------------|
| 1      | Initial screening | 2 -3 hours  | Lab tests only            |
| 2      | Inclusion 0 weeks | 2 – 3 hours | Motivation and Counseling |
| 3      | 1 month after inclusion  | 1 hour             | Motivation and counseling        |
| 4      | At 2 months              | 1 hour             | Motivation and counseling        |
| 5      | At 3 months              | 1 hour             | Motivation and counseling        |
| 6      | At 4 months       | 3 hours     | Motivation and Lab Tests  |
| 7      | At 5 months              | 1 hour             | Motivation and counseling        |
| 8      | At 6 months              | 1 hour             | Motivation and counseling        |
| 9      | At 7 months              | 1 hour             | Motivation and counseling        |
| 10     | At 8 months              | 1 hour             | Motivation and counseling        |
| 11     | At 9 months              | 1 hour             | Motivation and counseling        |
| 12     | At 10 months             | 1 hour             | Motivation and counseling        |

|    |              |         |                           |
|----|--------------|---------|---------------------------|
| 13 | At 11 months | 1 hour  | Motivation and counseling |
| 14 | At 12 months | 3 hours | Motivation and Lab Tests  |

### Control group

The subjects in the control group will be educated regarding general principles of a healthy lifestyle based on the religious sermon (khutbah) that benefits T2DM prevention and informed about the current evidence showing that the lifestyle intervention is effective for T2DM prevention during the “run-in” period. After the inclusion and collection of baseline data, they will visit the study site at 4 months and 12 months for the collection of anthropometric, clinical, and laboratory investigations.

## 11. Data collection

### Phase 1: Pre-screening contact

The Imams will discuss and convey the message about the study program to the congregational participants during the Friday sermon. Any interested individual (including both male and female) aged 25 -65 years will be invited for risk assessment. A group of trained personnel of BADAS will assess the participant’s risk for T2DM by using the non-invasive risk score developed by BADAS. All individuals aged 25-65 years with a diabetes risk score  $\geq 9$  will participate in the screening visit. Individuals will be advised to fast overnight for at least 8-14h before the screening visit.

### Phase 2: Sample survey and collection of other data

Prior to initiating the survey, the study team will organize a comprehensive training program for Imams and female assistants at BADAS’s tertiary hospital (BIRDEM Hospital) in Dhaka, complemented by hands-on training sessions at the study sites. Local volunteers will be recruited and will receive standardized training covering data collection, intervention implementation, and participant monitoring. The training curriculum will include modules on diabetes prevention, lifestyle modification, and the effective use of educational materials. To ensure adherence to study protocols, volunteers will be closely supervised by the specialized research team.

A multidisciplinary team will be formed, consisting of four diabetologists, four dieticians, two health educators, one IT specialist, two eye technicians, and six phlebotomists. This team will be responsible for overseeing data collection at baseline, 4 months, and 12 months. The team will undergo an intensive weeklong training to standardize data collection procedures. Compliance with study protocols will be rigorously monitored through regular audits conducted by data safety officers, while independent evaluators, blinded to group assignments, will carry out outcome assessments to reduce bias and enhance the reliability of findings.

### Study plan/timetable

The proposed study will be implemented following the timetable as below:

| Procedure                     | Visit 1      | Visit 2  | Visit 3   |
|-------------------------------|--------------|----------|-----------|
| Timing                        | At screening | 4 months | 12 months |
| Informed consent              | X            |          |           |
| Check eligibility criteria    | X            |          |           |
| Record basic demographic data | X            |          |           |
| Dietary questionnaire         | X            | X        | X         |

|                              |   |   |   |
|------------------------------|---|---|---|
| Health questionnaire         | X | X | X |
| Knowledge questionnaire      | X | X | X |
| Economic questionnaire       | X |   |   |
| Blood pressure               | X | X | X |
| Anthropometric measurements  | X | X | X |
| Foot examination             | X | X | X |
| Collect venous blood samples | X | X | X |
| ECG                          | X | X | X |
| Randomization                | X |   |   |
| Run-in                       | X |   |   |
| Adverse event recording      | X | X | X |

#### **Informed consent:**

Full informed consent will be obtained. All potential participants will be given adequate time to read participant information sheets and had a chance to ask questions to satisfy any queries they have before consent. Staff members taking consent must assess whether potential participants have fully understood the information they provided before taking consent. Those who are not thought to be fully informed will not be included in the trial. All staff members taking consent will be trained in this procedure.

#### **Registration**

This will be included informed consent and completion of a detailed medical eligibility questionnaire. The eligibility screening questionnaire will be based on the inclusion/ exclusion criteria described above. If eligible, subjects have to finish the baseline survey at the same time. At the baseline survey, all participants will complete an interview-administered questionnaire and undergo a physical examination. They will also complete the 24-h food records using dietary record collections will be taught by trained investigators.

#### **Run-in**

A one-week “run-in” period followed the baseline survey during which two classes on general principles of lifestyle intervention for the prevention of T2DM will be taught. The specific lifestyle intervention program will not begin during this period. If an individual diagnosed with T2DM (fasting glucose  $\geq 7.0$  mmol/l or 2-h glucose  $\geq 11.1$  mmol/l) in our baseline OGTT test, we would exclude them from the present study at this period.

#### **Development of interviewer-administered questionnaires**

Before the study, a panel of experts will be agreed on a structured questionnaire after thorough discussions and also in the light of surveys conducted in previous studies. The panel will be included an endocrinologist, a diabetologist, a statistician, and a public health expert. The questionnaire will be developed by consulting existing information and clinical practices. The questionnaire will be developed in the local language of Bangla. Before the start of the study, pretesting of the questionnaire will be conducted to test its feasibility and reliability. As a result, a few minor modifications will be made after the pilot testing. Trained investigators will be collected data after face-to-face interviews with the participants. To assuring quality control, intensive training will be provided for the investigators to reduce bias as much as possible.

#### **Sample survey**

Upon arrival at the field sites, different sets of investigations and physical examinations will be done for each of the subjects taking part in the study. At first, an initial fasting blood sample will be taken. Then all the subjects will be given 75-gram oral glucose to drink and will be requested to wait for 2-hours for the second

blood sample collection. During this 2-hour waiting time, socioeconomic and demographic information, and parental and personal health histories will be verbally obtained using standardized questionnaires. After completion of the interview, the anthropometric measurements including height, weight, hip and waist circumference (WC) will be taken. Also, blood pressure (BP) will be recorded at this time followed by a physical examination. These will be carried out through trained personnel. After 2 hours, a second blood sample for OGTT will be collected.

### **Anthropometrical measurements**

Anthropometric measurements including height, weight, and waist and hip circumferences will be taken with the subjects wearing light clothes and without shoes. Weight will be recorded to the nearest 0.1 kg using electronic digital LCD weighing machines (Best Deluxe Model; Bathroom, Dhaka, Bangladesh) placed on a flat surface. The scales will be placed on a flat surface and calibrated using a standard (20 kg) each day. Height will be taken while the subjects stood in the erect posture, touching the occiput, back, hip, and heels on a straight measuring wall, while the subjects looked straight ahead. Body mass index (BMI) will be calculated as the weight (Kg) divided by the square of the height ( $m^2$ ). WC will be measured by placing a plastic tape horizontally midway between the lower border of the ribs and the upper border of the iliac crest on the mid-axillary line. Hip circumference will be measured to the nearest centimeter at the greatest protrusion of the buttocks. Waist-hip ratio (WHR) will then be calculated from WC (cm) and height (cm), respectively.

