### **10.3 Inclusion Criteria**

- All individuals aged 25-65 years with diabetes risk score  $\geq 9$  [32] and diagnosed with prediabetes (IFG/IGT) as per WHO recommended diagnostic value [33]. These are the primary inclusion criteria.
- Both Gender
- Permanent residents
- Willing to participate and available for 12 months of study

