### **10.5 Study variables**

- **Socio-demographic variables:** age, sex, economic status, education status, smoking habit, lifestyle (physical activity and food habit).
- **Anthropometric variables:** height, weight, body mass index (BMI), waist circumferences (WC), waist-height ratio (WHR), and waist-height ratio (WHtR).
- **Clinical & Biochemical variables:** blood pressure, fasting blood glucose (FBG), 2-hour blood glucose, HbA1c, fasting lipid profile, ECG and fundus photography.
- **Quality of Life:** Assessed using the EuroQol-5D-5L scale and EuroQol-VAS score.
- **Diabetes Knowledge:** Assessed through structured questionnaires.
- **Economic Variables:** employment status, productivity loss (income and days/hours of work lost), out-of-pocket payments (OPP), the opportunity cost of time (average wage and time), borrowing/selling assets, expenditure.

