## Definition of terms

- DM will be defined as if FPG  $\geq 7.0$  mmol/L or 2hPG  $\geq 11.1$  mmol/L. Prediabetes will be defined as FPG  $\geq 6.1$  mmol/L to  $< 7.0$  mmol/L (impaired fasting glycemia, IFG) and 2hPG  $\geq 7.8$  mmol/L to  $< 11.1$  mmol/L (impaired glucose tolerance, IGT). Normal glucose tolerance (NGT) will be defined as FPG  $< 6.1$  mmol/L and 2hPG  $< 7.8$  mmol/L. For screening of NGT, prediabetes, and DM, diagnostic criteria of WHO in 2006 will be used [33].

- Cut off points for general obesity for both sexes will be defined as BMI of  $\geq 25 \text{ kg/m}^2$  [35] and central obesity including WC for men and women will be  $\geq 90$  and  $\geq 80$  cm [34], and WHR for men  $\geq 0.90$  and women for  $\geq 0.80$  [36], respectively.
- Hypertension will be defined as systolic blood pressure (SBP) of 140 mm Hg or diastolic blood pressure (DBP) of 90 mm Hg or current treatment with antihypertensive medication [37].
- Cut-off values for serum lipid profiles will be high cholesterol (T-Chol)  $\geq 5.0 \text{ mmol/L}$ , high triglycerides (Tg)  $\geq 1.7 \text{ mmol/L}$ , high LDL-C  $\geq 3.4 \text{ mmol/L}$  and low HDL-C  $< 1.04 \text{ mmol/L}$  (for men) and  $< 1.3 \text{ mmol/L}$  (for women) [38].
- Dyslipidaemia will be defined as serum triglycerides  $\geq 1.70 \text{ mmol/L}$  for both sexes and HDL-C  $< 1.04 \text{ mmol/L}$  for men and  $< 1.3 \text{ mmol/L}$  for women [37].
- Bangladesh Diabetes Risk Score (BDRS) will be developed based on multiple logistic regression analysis using five simple parameters namely age ( $\leq 30 = 0$ ,  $31-40 = 3$ ,  $\geq 41 = 4$ ), sex (female = 0, male = 2), BMI ( $< 25 \text{ kg/m}^2 = 0$ ,  $\geq 25 \text{ kg/m}^2 = 2$ ), WHR (m  $< 0.90$ ; f  $< 0.80 = 0$ , m  $\geq 0.90$ ; f  $\geq 0.80 = 5$ ), and presence of HTN (no = 0, yes = 2). Subjects with a BDRS of  $< 5$  was categorized as low risk, 5 to 9 as medium risk and  $> 9$  as high risk for T2DM [32].
- Smoking habits will be classified as either current or non/ex-smoker.
- Socio-economic condition will be classified as low ( $< 5000$  Bangladeshi Taka [BDT, 1 USD = 84 BDT]), medium (5000-1000 BDT) and high ( $> 10000$  BDT) based on the monthly expenditure.

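### The protocol's only formula for waist-hip ratio divides waist by height; probably a drafting slip, but the ratio carries 5 points of the entry score and must be corrected as written

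*Combined protocol and SAP*

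**What the plan says.** Three parts of the protocol bear on this ratio.

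- **Section 11, Anthropometrical measurements.** Hip circumference is taken: "Hip circumference will be measured to the nearest centimeter at the greatest protrusion of the buttocks". The next sentence leaves it out: "Waist-hip ratio (WHR) will then be calculated from WC (cm) and height (cm), respectively".
- **Section 10.5, Study variables.** The anthropometric list ends "waist-height ratio (WHR), and waist-height ratio (WHtR". One name carries two abbreviations, and waist-hip ratio is not listed.
- **Section 11, Definition of terms.** WHR cut-offs of 0.90 for men and 0.80 for women define central obesity, alongside separate waist cut-offs of 90 cm and 80 cm. The same WHR cut-offs enter the risk score: "Bangladesh Diabetes Risk Score (BDRS) will be developed based on multiple logistic regression analysis using five simple parameters". No formula for WHR is given there.

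The score decides entry. Section 10.3 requires 9 or more together with prediabetes and adds "These are the primary inclusion criteria". Under Phase 1 (Pre-screening contact), people aged 25 to 65 who score 9 or more "will participate in the screening visit". The SAP does not define WHR.

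**The concern.** The name says waist-hip, the formula says waist-height, and the variable list sides with the formula. The documents contain no correct definition that overrides the wrong one.

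In most protocols a mislabelled body-size index would be cosmetic. Here it is the largest single item in a score that is a primary inclusion criterion, and the cut-offs do not fit waist/height. Anyone who scored participants from the written formula would withhold 5 points from most people entitled to them, and the loss would fall much harder on women than on men. The trial enrols both sexes, has the imams promote female participation during recruitment, provides a separate venue for women, and has a sex subgroup in SAP section 8. A reader should be able to tell from the documents which ratio governed entry, and at present cannot.

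**Working it through.** The plan states no figure on this point to reproduce. The check is an enumeration of the score.

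**Inputs (Definition of terms; section 10.3).** Age: 30 or under = 0, 31 to 40 = 3, 41 or over = 4. Sex: female = 0, male = 2. BMI of 25 or more = 2. Hypertension = 2. WHR at or above 0.90 (men) or 0.80 (women) = 5. Entry at 9 or more. Within each sex, 3 age bands × 2 BMI levels × 2 hypertension levels give 12 profiles.

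**Step 1. Who reaches 9, with and without the WHR points.**

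| | Maximum | Profiles at 9 or more |
|---|---|---|
| Women, no WHR points | 4 + 0 + 2 + 2 = 8 | 0 of 12 |
| Women, WHR points | 8 + 5 = 13 | 8 of 12 |
| Men, no WHR points | 4 + 2 + 2 + 2 = 10 | 2 of 12 |
| Men, WHR points | 10 + 5 = 15 | 11 of 12 |

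The two male profiles without WHR points are age 31 to 40 with both other factors (3 + 2 + 2 + 2 = 9) and age 41 or over with both (10). With the points, a woman aged 41 or over qualifies on age and WHR alone (4 + 5 = 9). A woman therefore cannot enter without the WHR points.

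**Step 2. What it takes to earn the points on waist/height.** Waist needed = cut-off × height.

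- Women: 0.80 × 140 = 112 cm; 0.80 × 150 = 120 cm; 0.80 × 160 = 128 cm.
- Men: 0.90 × 160 = 144 cm.

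For comparison, a woman 150 cm tall at the protocol's own central-obesity waist of 80 cm has waist/height 80/150 = 0.53. At a waist of 100 cm it is 100/150 = 0.67. A man 160 cm tall at the 90 cm waist cut-off has 90/160 = 0.56. The 0.80 and 0.90 thresholds are far out of line with waist/height.

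**Step 3. How rare a waist/height of 0.80 is in women.** The documents give no body-size distribution, so these are assumptions: independent normal waist and height, height mean 150 cm and SD 6 cm, 4,000,000 simulated women per row.

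| Assumed waist mean (SD), cm | Share with waist/height of 0.80 or more |
|---|---|
| 80 (10) | 0.02% |
| 85 (11) | 0.2% |
| 90 (12) | 1.0% |
| 95 (13) | 3.6% |

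**Step 4. Direction of the error.** Height exceeds hip circumference in essentially everyone, so waist/height is smaller than waist/hip. The written formula can only lower a score. Anyone at 9 or more on waist/height is also at 9 or more on waist/hip, so the error could exclude people wrongly but could not admit them wrongly.

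**The case against.** The strongest reply is that the sentence corrects itself. It names the index waist-hip ratio and follows directly on the hip measurement. It ends in a stray *respectively* that suits a sentence once listing two ratios. Section 10.5 carries two abbreviations, so two indices were intended, and the cut-offs make sense only for waist/hip. That is persuasive as to intent, and a drafting slip is the likely explanation. It does not remove the defect, because the only formula on the page is wrong and the variable list repeats it.

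A second reply is that the anthropometry section describes measurements taken during the glucose-test wait, whereas the score is first applied at pre-screening by trained staff using an existing published score. This stands as a limit. The link between the formula and the entry score is the shared term WHR, and nothing says that the pre-screening score was computed from that sentence.

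A reader might go further and infer that women were in fact largely kept out. The documents do not support that. SAP section 4 reports 799 participants in the final sample with cluster sizes of 92 to 110, and section 8 reports a sex subgroup as carried out. Without counts by sex this is not proof, but it fits poorly with an almost all-male sample. A reader might also infer that the 5-point item would be wrong for nearly everyone. It would not: people truly below the waist-hip cut-off score 0 either way. Only those at or above it would lose points, and their share is not given.

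**Conclusion.** The point holds as a rule that gives a wrong result if followed as written. Used in the score, waist/height would remove 5 points from nearly everyone who truly meets the waist-hip cut-off. It would cap women at 8, one point short of entry, and leave men 2 of 12 profiles instead of 11. WHR-defined central obesity would be understated in the same way.

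The cap of 8 and the profile counts are exact from the protocol's own points. The statement that almost no woman could enter rests on the assumed body sizes above, under which about 0.02% to 3.6% of women would reach 0.80 on waist/height. The whole consequence is conditional on the written formula having been used for the score, which the documents neither state nor rule out. It should be corrected, but it is not evidence that enrolment went wrong.

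**What to change.** **Wording.**

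- In Anthropometrical measurements, define WHR = waist (cm) / hip (cm) and WHtR = waist (cm) / height (cm).
- In section 10.5, expand WHR as waist-hip ratio.
- In Definition of terms, add one sentence saying that the BDRS and the WHR criterion for central obesity use waist/hip.

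**Check of what was applied.** Compute the BDRS both ways for enrolled participants. Report, by sex, how many reach 9 on waist/hip but not on waist/height. For women, who cannot reach 9 without the WHR points, these are the enrolled women with waist/height below 0.80. Many such participants would show that waist/height was not used at entry.

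Counting enrolled participants whose recomputed waist/hip score falls below 9 would not help, because by Step 4 this error cannot produce any. The people it could harm are those screened out, so where their measurements were kept, recompute their BDRS on waist/hip as well and report by sex how many reach 9.

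**Cost.** Two wording corrections, one added sentence, and a short calculation. Waist, hip and height are all scheduled to be recorded for participants. Whether values for people screened out were kept is not stated.
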